#### Clinical Data

For both the retrospective and prospective study, data will be collected from the electronic patient records and trauma registry (Network Emergency Care Brabant). The trauma registry compiles prehospital and hospital data of all trauma patients admitted after presentation to the emergency department. Patients with splenic injury will be identified by the International Statistical Classification of Disease and Related Health Problems (ICD-10) and Abbreviated Injury Scale (AIS) diagnosis codes starting with S36.x and 5442, respectively.

The collected data concern the following: age, sex, systolic blood pressure, hemoglobin, Glasgow coma scale (at arrival), intubation (Yes/No), imaging (US and/or CT), grading spleen injury (American Association for the Surgery of Trauma; see Table 2)[28], type of treatment (NOM/SAE/splenectomy), complications, hospital stay (days), spleen in situ at discharge (Y/N), reinterventions (Y/N), rehospitalization (Y/N), and mortality.

**Table 2 table2:** American Association for the Surgery of Trauma spleen injury scaling (1994 Revision).

Grade^a^		Injury description
**I**		
	Hematoma	Subcapsular <10% of surface area
	Laceration	Capsular tear <1 cm parenchymal depth
**II**		
	Hematoma	Subcapsular 10%-50% of surface area; or intraparenchymal <5 cm in diameter
	Laceration	1-3 cm parenchymal depth, which does not involve a trabecular vessel

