### Statistical Analysis

All analyses will be conducted using SPSS V24.0 (Statistical Package for Social Sciences, Chicago Illinois, USA). Frequencies and descriptive statistics will be calculated to provide an overview of the characteristics of the study population. Statistical test results will be considered significant at a level of *P*<.05.

Concerning the retrospective study, a MANCOVA will be done after correcting theoretically important covariates to assess the differences between treatment groups on the 4 WHOQOL-Bref domains and the general facet. For each type of treatment, a 1 sample *t* test will be performed for each WHOQOL-Bref scale to compare the QOL scores with reference data.

For both the retrospective and prospective studies, a logistic regression analysis will be performed on the outcome variables’ (1) need for reintervention (yes/no) and (2) for each complication (yes/no), assessing the effect of treatment after correcting for theoretically important covariates. With regard to hospital stay in days, a Kruskal-Wallis test will be performed with the group (type of treatment) and days in hospital. Analysis of covariance will be used to compare proximal versus distal SAE, thereby correcting the effect for theoretically important covariates. To confirm/find prognostic factors for failure of NOM, a logistic regression analysis will be performed if NOM is a failure quickly after treatment. Otherwise, a survival analysis will be performed.

Regarding the prospective study, to assess the differences between groups in their change in QOL over time, a linear mixed model analysis will be conducted. To answer our research question, we will focus on the interaction effect between measurement occasion and treatment group, while correcting for theoretically important covariates. For the repeated measures, an unstructured covariance matrix will be used. Item-level missing values will be imputed according to the guidelines of the questionnaires. Scale-level missing values will be handled directly through maximum likelihood estimation, because the mixed model procedure makes use of all available data for each participant over all time points.

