To conduct the cost-effectiveness analysis, a cost-effectiveness model will be developed. This model will comprise 2 treatment arms; SAE will be compared with splenectomy. The cost-effectiveness study will be conducted according to the most recent Dutch guidelines for health economic research [54]. As such, the study will be performed from the societal perspective, which means that all costs and benefits should be considered, regardless of by whom the costs are borne or to whom the benefits accrue.

Effects will be expressed in quality-adjusted life years, which constitute a combination of QOL and length of life. QOL will be measured in utilities. Utilities express QOL on a scale from 0 (death) to 1 (perfect health). Utilities can be derived from the EQ-5D-5L [44]. Survival will be derived from international clinical literature. Costs will be estimated according to the Dutch Manual for Costing in Economic Evaluations, update 2015, using a societal perspective [54]. A bottom-up methodology will be used to compute costs; the total number of medical contacts will be multiplied with unit costs. Direct medical costs comprise all costs directly relating to the prevention, diagnostics, therapy, rehabilitation, and care of the intervention. Health care utilization will be derived from the iMCQ [52]. The iPCQ will be used to assess productivity losses [51]. The friction cost method will be used for the calculation of costs because of production losses [55]. This method is the expertise of the iMTA; it is its standard method and has been widely used.

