Several factors related to the design and execution must be taken into account. First, patients will be treated with NOM, SAE, or surgery for a specific clinical condition. It may be the clinical situation that determines the long-term outcome, although that outcome is not or partially the result of the treatment. This risk is confounding by indication: the risk that the groups are in fact not easily comparable (ie, selection bias). To keep this to a minimum, the reason for choosing a particular treatment will be registered. In our analysis, we will correct for these confounding factors using propensity score analysis. Correction is only possible when adequate and good-quality information is available about the clinical condition of the patients, which led to the decision. The patient’s record will be searched thoroughly to find this information. Second, trauma patients often have multiple injuries that can affect QOL and clinical outcomes. We are not primarily interested in these additional injuries, but these will be included as a covariate in the analysis. Third, response bias may occur in the questionnaires group. Patients may decline participation because they are not interested or it may be too confronting to think/correspond about their psychological state. Fourth, the severely injured patients may be overrepresented in the nonresponse group concerning the questionnaires. To limit this, these patients will be visited as soon as they are approachable and, if necessary, will be provided assistance to complete the questionnaires. Fifth, the absence of randomization is a (strong) limitation and a potential source of bias, but randomized comparison in managing trauma patients is virtually impossible. Furthermore, it will have strong ethical implications as it is well known that randomizing trauma patients with intraabdominal bleeding, potentially unstable, is something not feasible in clinical practice. Sixth, the sample size calculation is based on the primary objective of the study. For the clinical and cost-effectiveness analysis, this implies that because of the small sample size, the uncertainty about the outcome is large. Seventh, we are aware of response shift bias. Response shift is a change in self-reported QOL that is a result of a change in internal standards (ie, recalibration), values (ie, reprioritization), or meaning of QOL (ie, reconceptualization) [56,57]. Thus, response shift reflects psychological adaptation: we do not consider this as a problem but as a fact of life. In addition, the method to prevent response shift contains recall bias itself. Considering this, and the fact that QOL is a generic outcome measure, ensures that we use the chosen method. Moreover, the retrospective patients will not be included in the prospective study.

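### Hospital stay is compared across treatments with a Kruskal-Wallis test, which cannot carry the confounding correction the protocol promises, so a significant result can reflect case mix

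*Protocol article*

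**What the plan says.** The Statistical Analysis section of the protocol article fixes the method for stay in one sentence: "With regard to hospital stay in days, a Kruskal-Wallis test will be performed with the group (type of treatment) and days in hospital". No covariate, weight or matching step is named. The sentence before it, on reintervention and complications, specifies logistic regression "assessing the effect of treatment after correcting for theoretically important covariates". The sentence after it, on proximal versus distal embolization, specifies analysis of covariance, "thereby correcting the effect for theoretically important covariates". The retrospective MANCOVA and the prospective mixed model in the same section carry a similar correction.

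The Discussion sets out why correction is needed: "This risk is confounding by indication: the risk that the groups are in fact not easily comparable (ie, selection bias". Its remedy is general: "In our analysis, we will correct for these confounding factors using propensity score analysis". It adds that trauma patients often have other injuries that can affect both QOL and clinical outcomes, and that "these will be included as a covariate in the analysis".

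Two other places show that the groups differ by design. The Abstract (Methods) says treatment depends on the severity of the splenic injury, the patient's hemodynamic condition, and local preference. The Background describes nonoperative management (NOM) as standard care in stable patients. It describes surgery as indicated in unstable patients who do not respond to transfusion, or when associated abdominal injuries require an operation.

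**The concern.** Length of stay is an outcome on which severity and associated injuries can be expected to act directly, and the same factors decide who gets NOM, splenic artery embolization (SAE) or splenectomy. A test with no place for those factors compares three case mixes as much as three treatments. The protocol recognizes this problem in general terms and corrects for it in its other models, but names a method for stay that cannot do so.

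What is at stake is a secondary clinical result. The Study Design section says the study assesses the effects of the three treatments, and the Objectives aim at selection criteria for a management guideline. A significant unadjusted difference in stay could be cited in that argument although severity alone produced it.

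**Working it through.** **Step 1. The methods side by side (Statistical Analysis section).**

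| Comparison | Method | Correction stated |
|---|---|---|
| WHOQOL-Bref by treatment, retrospective | MANCOVA | yes |
| Reintervention, each complication | logistic regression | yes |
| Hospital stay by treatment | Kruskal-Wallis | none |
| Proximal versus distal SAE | ANCOVA | yes |
| Change in QOL by treatment, prospective | linear mixed model | yes |

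The one-sample *t* tests compare with reference data, not between treatments, so they are left out.

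**Step 2. What the test can use.** The statistic is H = [12 / (N(N+1))] × Σ(R_j² / n_j) − 3(N+1), where R_j is the rank sum and n_j the size of group j. Only ranks of stay and group labels enter. Neither additional injuries nor a propensity score can be added as a term.

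**Step 3. The plan's own figures.** The protocol gives no sample size or effect for stay. Its sizes of 138 (retrospective) and 33 (prospective) are for QOL and are used here only for scale.
- 138: Pillai trace, 3 groups, 5 responses, f² = 0.061, df1 = 10, df2 = 2(138 − 6) = 264, λ = 2 × 138 × 0.061 = 16.8. Power is 0.801, so 138 is reproduced.
- 33: f = √(0.05/0.95) = 0.229, df1 = 8, df2 = 4(N − 3), λ = f² × N × 5/(1 − 0.5). This gives 31 (power 0.807), close to the stated 33.

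**Step 4. Illustration with no treatment effect.** All inputs here are assumptions, except alpha = 0.05 and the two values of N.
- Severity x is standard normal.
- Treatment comes from a·x + √(1 − a²)·e, with e standard normal, cut at 0.25 and 0.84 (shares about 60/20/20).
- Stay in whole days is exp(2 + 0.7·[b·x + √(1 − b²)·u]), rounded, with u standard normal. The median is about e² = 7.4 days, and there is no treatment term.
- The adjusted comparison is a rank ANCOVA on severity: F = [(RSS0 − RSS1)/2] / [RSS1/(N − 4)].
- There are 2,000 replicates per row. The Monte Carlo standard error at 5% is √(0.05 × 0.95/2000) = 0.5 percentage points.

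| a (severity–treatment) | b (severity–log stay) | N=138 unadjusted | N=138 adjusted | N=33 unadjusted | N=33 adjusted |
|---|---|---|---|---|---|
| 0 | 0.5 | 5.0% | 5.5% | 4.3% | 4.6% |
| 0.3 | 0.3 | 11.0% | 5.5% | 5.1% | 5.1% |
| 0.5 | 0.3 | 21.5% | 5.9% | 7.6% | 5.5% |
| 0.5 | 0.5 | 56.9% | 5.7% | 13.0% | 5.0% |
| 0.7 | 0.5 | 86.3% | 5.9% | 25.9% | 4.8% |

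The first row is a control: when severity does not drive treatment, the unadjusted test keeps its level. With a = b = 0.5 and N=138, median stays average 6.6, 8.2 and 9.6 days, a gap of 9.6 − 6.6 = 3.0 days from severity alone.

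Two limits apply. At N=33, replicates with a group below three patients were skipped but kept in the denominator. For a 20% group the chance of this is 0.8³³ + 33 × 0.2 × 0.8³² + 528 × 0.04 × 0.8³¹ = 0.027, so about 5% for the two small groups. The 13.0% would be about 13.0/0.95 = 13.7% without that. Also, the adjusted column corrects for the exact severity variable, which is a best case.

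**The case against.** **The propensity sentence in the Discussion is not restricted to named outcomes.** A rank test can be run in a propensity-matched sample or within strata, and how the score enters each outcome is normally left to an analysis plan. This is the strongest reply, and part of it stands: the two sections could be reconciled that way. But the article does not say so. It writes down a plain test of group against days, between two sentences that do state a correction. Matching would also not make additional injuries a covariate in this test.

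**Kruskal-Wallis is a valid test of whether the stay distributions are equal.** If case mix makes them differ, rejecting is correct and is not a type I error. That also stands. The percentages above measure a wrong conclusion only if the result is taken as an effect of treatment. The sentence on stay makes no such claim, and the Discussion warns that the clinical situation may determine outcome. A reader might infer that severity will be reported as a treatment effect; the text supports only that it can be.

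**Wider readings are tempting but not supported.**
- That the same bias enters the cost model, where "SAE will be compared with splenectomy". The article takes health care use from the medical consumption questionnaire, nothing feeds the stay test into that model, and its silence on adjustment is ordinary in a condensed article.
- That the severity data are missing. The list beginning "The collected data concern the following: age, sex, systolic blood pressure, hemoglobin, Glasgow coma scale (at arrival" also includes intubation and spleen grade, and the Discussion commits to registering the reason for treatment and to including additional injuries.
- That the QOL comparisons between treatments are biased in the same way. They are stated to be adjusted.
- That early deaths will be counted as short stays. The article does not say how in-hospital deaths are handled.

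**Conclusion.** The point holds in a limited form. The protocol names for hospital stay a method that takes no covariates, while its other models comparing treatment groups are corrected and its Discussion promises correction for confounding by indication. If the stated test is followed, a significant result cannot be separated from case mix.

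The size is illustrative. Under assumed correlations of 0.3 to 0.5 and no treatment effect, rejection is roughly 11 to 57% at N=138 and 5 to 13% at N=33, against about 5 to 6% after adjustment. With weak confounding and a small sample the problem is negligible; with stronger confounding it is large. The documents give neither the correlations nor the N for stay. Clinical data in the retrospective study come from all splenic injury patients, so 138, a requirement for the QOL analysis, is not that N.

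Hospital stay is a secondary clinical measure, so this does not threaten the primary QOL comparisons. It is worth correcting because the remedy is simple and uses information the study already collects or commits to collect.

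**What to change.** Make the treatment comparison of hospital stay a regression using the same covariates or propensity weights as the other clinical outcomes. A log-linear model, a negative binomial model, or time to discharge alive with death as a competing event would each serve. The last also settles how in-hospital deaths count. Keep the Kruskal-Wallis test as a description of unadjusted differences, labeled as such. If the intention was a rank test in a propensity-matched or stratified sample, say so in the Statistical Analysis section and state how additional injuries are handled.

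The cost is one additional model, with no new patient contact. Residual confounding will remain to the extent that recorded severity and the reason for treatment are incomplete, a limit the Discussion already acknowledges.

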### Objectives

There is a growing demand for a (national) guideline or protocol for clinical decision making in traumatic spleen injury. Therefore, it is important to determine the optimal selection criteria for the appropriate management strategy. To achieve this, the entire process surrounding a patient with splenic injury must be considered. Even today, it remains unclear what the impact of QOL is on the entire process. Therefore, the primary objective of this project is to examine the QOL of patients after therapy (NOM, SAE, and surgery) for traumatic spleen injury using a retrospective and prospective group of patients. The secondary objective is to investigate the clinical outcome (eg, complications, reinterventions, and additional therapy), imaging outcome (diagnosis and magnetic resonance spleen imaging after SAE), and cost outcome (cost-effectiveness) and their relation to QOL.

Finally, the data and results acquired from this study may result in the development of a patient-oriented protocol for the management of traumatic spleen injury.

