### Sample Size Calculation

As the World Health Organization QOL assessment instrument-Bref (WHOQOL-Bref) comprises multiple facets, the *retrospective data* will be analyzed using a multivariate analysis of covariance (MANCOVA). This technique is more powerful than a univariate analysis of variance, resulting in a required sample size of 135 patients giving a medium effect and power of 0.80. Previous research [26] indicates that the minimal clinically important difference (MCID) of the WHOQOL-Bref slightly varies across its domains. Table 1 shows for each domain the MCID and standard deviation. On the basis of these statistics, the Cohen *d* effect sizes were calculated and transformed via Cohen *f* to the *f*^2^ effect sizes required in the MANCOVA power analysis. It turns out that 138 participants are required to detect the average *f*^2^ of 0.061 with a power of 0.80, given a significance level of .05.

With regard to the *prospective data*, mixed linear modeling will be used. Power analysis is performed for a repeated measures design investigating the interaction between treatment and time. We assumed a significance level of .05 and a medium effect size of partial eta squared of 0.05 and an average correlation of 0.50 among the 5 repeated measurements. On the basis of this, we require 33 participants to test with a power of 0.80, whether the 3 treatment groups differ in their change in QOL over the follow-up time. When assuming an effect size similar to the MCID’s reported in the table above, 27 participants are required to detect the medium effect of *f*=0.248 with a power of 0.80.

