#### Prospective Study

In each participating hospital, an interventional radiologist and a trauma surgeon will be designated as principal investigators. Each hospital will also have a research assistant, most likely a radiology technologist or a member of the research team. The daily work will be carried out by the research assistant under the supervision of the principal investigator at the ETZ Hospital (CR). The research assistant will check daily whether potential eligible patients were admitted to the hospital. This will be done by checking the subscription list, verbally checking with the attending (resident) radiologist and trauma surgeon, and verifying the data in the electronic patient record. The subscription list will be placed at the dictation station of the radiologist, where the trauma diagnoses are reported. If a patient is treated for a traumatic spleen injury, baseline characteristics will be collected and he/she will be screened for the inclusion and exclusion criteria. The clinical data of all eligible patients will be collected anonymously in the database. As soon as the patient can talk and is lucid, the assistant will visit the patient to provide a verbal and written explanation about the study. The time for consideration of participation is 1 week. When a patient is willing to participate, he/she will sign a consent form. If not, the reason will be noted if the patient wants to let it be known. Each inclusion will be reported to the principal investigator (CR). Total follow-up time is 1 year after treatment with time points at 1 week and 1, 3, 6, and 12 months after treatment.

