##### iMTA Productivity Cost Questionnaire

The impact of disease on the ability of a person to perform work should be part of an economic evaluation when a societal perspective is applied. The iMTA Productivity Cost Questionnaire (iPCQ) is a generic, nondisease-specific questionnaire, and it is applied in national and international studies [51]. The questionnaire is currently available in more than 10 languages, including Dutch. Both indirect cost because of absenteeism and the productivity losses because of presenteeism (ie, sick, but working) are taken into account. A manual is available, containing information on the modular structure of the iPCQ and its scoring and valuation methods that are used for cost calculations. By applying productivity costs, the answers of the iPCQ can be monetized and, as such, used in health economic evaluations.

**Table 3 table3:** Timeline of the prospective study concerning measurements.

Time point	Timing and setting	Demographics	Questionnaires	Imaging
T1	After treatment, during admission	Demographic factors and clinical data	Quality of life (WHOQOL-Bref^a^); health status (SF-12^b^); and health-related QOL^c^ (EQ-5D-5L^d^)	—^e^
T2	1 month after treatment, at home (MRI^f^: outpatient clinic)	—^g^	Quality of life (WHOQOL-Bref); health status (SF-12); health-related QOL (EQ-5D-5L); productivity costs (iPCQ^h^); and medical consumption (iMCQ^i^)	MRI (SAE^j^ patients only)
T3	3 months after treatment, at home	—^g^	Quality of life (WHOQOL-Bref); health status (SF-12); health-related QOL (EQ-5D-5L); productivity costs (iPCQ); and medical consumption (iMCQ)	—^e^
T4	6 months after treatment, at home	—^g^	Quality of life (WHOQOL-Bref); health status (SF-12); health-related QOL (EQ-5D-5L); productivity costs (iPCQ); and medical consumption (iMCQ)	—^e^
T5	1 year after treatment, at home (MRI: outpatient clinic)	Clinical data	Quality of life (WHOQOL-Bref); health status (SF-12); health-related QOL (EQ-5D-5L); productivity costs (iPCQ); and medical consumption (iMCQ)	MRI (SAE patients only)

^a^WHOQOL-Bref: World Health Organization Quality of Life assessment instrument-Bref.

^b^SF-12: 12-Item Short-Form Health Survey.

^c^QOL: quality of life.

^d^EQ-5D-5L: Euroqol 5-Dimensional 5-Level questionnaire.

^e^At this time point, no MRIs have been completed.

^f^MRI: magnetic resonance imaging.

^g^At this time point, no demographic or clinical data have been collected.

^h^iPCQ: iMTA Productivity Cost Questionnaire.

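### The prospective study answers a question about QOL after each therapy with the treatment-by-occasion interaction alone, which is zero for a difference already present at the post-treatment T1 and constant afterwards

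*Protocol article*

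**What the plan says.** The Objectives section states that "the primary objective of this project is to examine the QOL of patients after therapy (NOM, SAE, and surgery) for traumatic spleen injury". For the prospective cohort, the Statistical Analysis section plans as follows: "to assess the differences between groups in their change in QOL over time, a linear mixed model analysis will be conducted". It then says that, to answer the research question, "we will focus on the interaction effect between measurement occasion and treatment group", with correction for covariates. The Sample Size Calculation section matches this: "Power analysis is performed for a repeated measures design investigating the interaction between treatment and time". It arrives at 33 participants (partial eta squared 0.05) or 27 (f = 0.248, taken from the MCIDs in Table 1).

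Every measurement comes after treatment: "Total follow-up time is 1 year after treatment with time points at 1 week and 1, 3, 6, and 12 months after treatment". Table 3 describes T1 as "After treatment, during admission". No pre-injury or recalled baseline is planned. The Discussion sets aside the approach to response shift because "the method to prevent response shift contains recall bias itself". A comparison of QOL level between treatments (MANCOVA) is named for the retrospective cohort only.

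**The concern.** The objective concerns how patients fare after each therapy, and the article wants the result to inform the choice of treatment. That is a question about level. The interaction asks something else: whether the gap between groups changes across occasions. With a pre-treatment baseline, change would carry the treatment effect. Here the first occasion is already post-treatment, so an effect that has appeared by T1 is absorbed into the reference measurement.

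Two misreadings could follow. A treatment that leaves patients one MCID worse at every visit gives a null result on the named test, which could be reported as no QOL difference. A treatment whose patients start worse and fully recover can give a significant result although QOL at 12 months is equal. Either could feed into the patient-oriented protocol that the study is meant to support.

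**Working it through.** **Inputs.** From Sample Size Calculation: alpha 0.05, k = 3 groups, m = 5 measurements, rho = 0.50, partial eta squared 0.05 (f² = 0.05/0.95 = 0.0526) or f = 0.248 (f² = 0.0615). From the average row of Table 1: d = 0.495. Assumed here: equal groups, compound symmetry, no covariates and no dropout.

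**1. The plan's own figures.** For the interaction, lambda = N·m·f²/(1 − rho), with df = (k − 1)(m − 1) = 8 and (N − k)(m − 1).
- Partial eta squared 0.05, N = 33: lambda = 33 × 5 × 0.0526/0.5 = 17.4, power 0.84. The minimum is N = 31, which becomes 33 with equal groups.
- f = 0.248, N = 27: lambda = 27 × 5 × 0.0615/0.5 = 16.6, power 0.81.

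Both stated sizes reproduce. The arithmetic is sound for the interaction.

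**2. Constant difference.** Let one group be shifted by the same amount at all five occasions. Each group-by-occasion mean minus its group mean is then the same in every group, so the interaction is exactly zero. Rejection rates in simulation:

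| Shift in one group | N | Interaction test | Group main-effect test |
|---|---|---|---|
| 0.5 SD, constant | 33 | 4.9% | 30% |
| 0.5 SD, constant | 138 | 4.9% | 90% |
| 0.5 SD, constant | 300 | 4.9% | 99.8% |
| 1.0 SD, constant | 33 | 5.2% | 86% |

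**3. Early difference that disappears.** One group has deficits of 1, 0.6, 0.3, 0.1 and 0 SD at T1 to T5, so the groups are equal at 12 months. The interaction test rejects in 54% of samples at N = 33 and in 99.8% at N = 138.

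**4. Power for level contrasts of one MCID.** With three groups and a range of d between the extreme means, f depends on the middle group. If it lies halfway, f = d/√6 = 0.408 × 0.495 = 0.202. If it equals one of the other two, f = (√2/3)d = 0.471 × 0.495 = 0.233. The degrees of freedom are 2 and N − 3 = 30.
- Averaged over visits: lambda = N·m·f²/(1 + (m − 1)rho) = 33 × 5 × f²/3 = 55f², that is 2.25 to 3.00. Power is 23 to 29%.
- At 12 months alone: lambda = N·f² = 33f², that is 1.35 to 1.80. Power is 15 to 19%.

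Using the article's own effect sizes directly, 80% power needs 99 (f = 0.248) to 114 (partial eta squared 0.05) participants for the visit-averaged contrast, and 162 to 189 for a single occasion.

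**5. Timing of T1 (illustration on assumed values).** Suppose QOL rises by 0.5 SD from 1 week to 1 month, linearly in log time. The slope is 0.5/ln(4.3) = 0.34 SD per log unit. If T1 falls on different days in two groups with no treatment effect, the apparent gap at T1 is:
- day 6 versus 8: 0.34 × ln(8/6) = 0.10 SD
- day 5 versus 9: 0.34 × ln(9/5) = 0.20 SD
- day 3 versus 14: 0.34 × ln(14/3) = 0.52 SD

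The documents give neither the slope nor the days. The range of about 0.1 to 0.5 SD shows what is possible, not what is expected.

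**The case against.** A reader might infer that any lasting difference between treatments is invisible to the prospective analysis. The documents do not support that. The mixed model also contains a treatment effect and yields adjusted means at each occasion, and focusing on the interaction does not exclude reporting them. A gap that emerges or widens after T1 does enter the interaction. The 5% rejection rate is the behaviour of a test under its own null, and nothing in the article says that an exactly constant gap is likely.

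There is also a case for the choice. Treatment is not randomized, and change contrasts remove the time-constant part of confounding by indication, which level contrasts retain. A group that starts worse and catches up shows a real difference in recovery, which the interaction is meant to show. Level is compared by MANCOVA in the retrospective cohort, so the two cohorts could be seen as sharing the work.

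These points limit the criticism but do not remove it. The article itself names the interaction as what answers its research question and sizes the cohort for that alone. The retrospective comparison is single-center, with one questionnaire per patient, and does not supply the prospective level comparison. Adjustment for confounders is already planned.

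On T1, 1 week and an in-hospital setting can coincide, and visit windows are often left to the full protocol. That makes timing a secondary point.

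**Conclusion.** The concern holds in this form: the named and powered prospective effect does not by itself answer the stated primary objective. The gap is exact for a difference already present at T1 and constant thereafter. It does not extend to differences that develop later, and it does not mean that level differences cannot be estimated.

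The stated 33 and 27 participants support 80% power for the interaction only, and the power for one-MCID level contrasts at N = 33 is low. Those power figures assume rho 0.5, equal groups and no covariates or dropout. The zero interaction under a constant shift depends on none of these.

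The T1 wording needs reconciling because patients are approached only once lucid, so actual timing may vary with severity, which also influences treatment. How much bias results cannot be determined from the article.

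**What to change.** 1. From the same mixed model, name the adjusted between-treatment differences in mean QOL, averaged over follow-up and at 12 months, with confidence intervals, as an answer to the primary objective alongside the interaction. Describe the interaction as the test of differing recovery courses, and state that a null interaction will not be read as no QOL difference.
2. Do not adjust these contrasts for T1, because treatment may already have affected it.
3. State that 33 and 27 participants give 80% power for the interaction only, and report the power of the level contrasts.
4. Reconcile T1 between the text (1 week) and Table 3 (during admission). Where completion dates are recorded, add a sensitivity analysis that uses actual days since treatment or omits T1.

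Cost: no new data and little extra analysis. The price is in interpretation. Level contrasts rest on the covariate and propensity adjustment already planned and will be imprecise at these sizes. The article reports enrollment as complete, so precision cannot be bought by recruiting more patients. Both kinds of contrast should therefore be shown.
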